### Assessments and outcomes

2.7

All assessments take place via the Caring Universities platform. At each time point, the participants receive a link to the assessment questionnaire via email. They get reminder emails to fill out the questionnaire 1 and 2 weeks after receiving the questionnaire. If they still don't fill it out, they will be called within a few days to remind them about the questionnaire. The reminder calls are made by the e-coaches, except for the anonymous participants who will be called by a researcher in the study. All outcomes and their time point measures are listed in Table 1.

**Table 1 t0005:** Time point measures of outcome assessments.

Outcome	Measure	Time of assessment					
		T0	T1	T2	T3	T4	T5
Socio-demographics	SR	X					
Procrastination	IPS	X		X	X	X	X
Depressive symptoms	PHQ-9		X	X	X	X	X
Stress	PSS		X	X	X	X	X
Anxiety	GAD-7		X	X	X	X	X
Quality of life	MHQoL		X	X	X	X	X
Satisfaction with treatment	CSQ-8			X		X	
Program usability	SUS-10			X		X	
Satisfaction with e-coach	WAI-I			X		X	
Treatment adherence	Number of modules completed		X	X	X	X	

Note: Abbreviations (alphabetical): CSQ-8: Client Satisfaction Questionnaire – 8 item version; GAD-7: Generalized Anxiety Disorder scale – 7 item version; IPS: Irrational Procrastination Scale; MHQoL: Mental Health Quality of Life questionnaire; PHQ-9: Patient health Questionnaire – 9 item version; PSS: Perceived Stress Scale; SR – self report measure; SUS-10: System Usability Scale – 10 item version; T0: eligibility screening – both groups; T1: baseline screening – both groups; T2: 4 weeks post baseline – intervention group; T3: 4 weeks post baseline – waitlist group; T4: 8 weeks post baseline – waitlist group; T5: 6 months post baseline – both groups; WAI—I: Working Alliance Inventory for guided internet interventions.

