#### Moderators and covariates

2.7.3

Previous studies have indicated that internet-based interventions rarely have a universal effect on all participants (Ebert et al., 2013; Karyotaki et al., 2018; Reins et al., 2021). Based on this, several socio-demographic variables and other program related variables will be assessed as potential covariates and moderators.

*Sociodemographic information* specifically age, gender, ethnicity, marital status, and whether the participant is currently receiving any psychotherapy or medication will be assessed as potential covariates.

*The Client Satisfaction Questionnaire* (*CSQ-8*) (Larsen et al., 1979) is used to measure the effects of participants' satisfaction with the overall intervention on the treatment outcome. The scale consists of eight items on a four-point Likert scale ranging from 1 (*low satisfaction*) to 4 (*high satisfaction*). The total scores can range from 8 to 32, with higher scores indicating greater satisfaction. The CSQ-8 has shown high reliability and validity for web-based interventions (Boß et al., 2016).

A single additional item is used to measure the participants' satisfaction with the individual modules of the intervention. At the end of each module the participants respond to the question “How useful was this module?” on a scale from 0 to 100, with higher scores indicating greater satisfaction with the module.

*System Usability Scale* (*SUS-10*) (Brooke, 1996) is used to measure the effects of program usability on treatment outcomes. It consists of ten items on a five-point Likert scale from 1 (*strongly disagree*) to 5 (*strongly agree*). The total scores range from 0 to 100 with higher scores indicating higher usability. The SUS-10 has become the most widely used standardized questionnaire to assess perceived usability and has shown good psychometric properties (reliability and validity) (Lewis, 2018).

*Adherence*, defined as “the degree to which the user followed the program as it was designed” (Donkin et al., 2011) is measured by dividing the number of main modules completed by a participant at time of post-test by the total number of main modules in the program, and multiplying this by 100 (Etzelmueller et al., 2020). The resulting percentage will indicate completion rate, with a higher value signifying greater treatment adherence.

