#### Primary outcome

2.9.1

Change in procrastination scores on the IPS will be assessed at post-treatment and follow-up assessments using multilevel mixed models linear regression with a restricted maximum likelihood algorithm for normally distributed data. Binomial models will be used for skewed data. The post-treatment score will be used as the dependent variable and trial arm condition (web-based transdiagnostic intervention vs WL) as independent while adjusting for baseline IPS scores. We will calculate the effect size of Cohen's d by subtracting the intervention group's average score on IPS measures from the average scores of the control group at the post- treatment and dividing the results by the pooled standard deviations. In addition, we will calculate the means and standard deviations of the groups at all time points. Analogously, the Cohen's d will be calculated for the difference score between the post-test measurement (t3 for the intervention group and t4 for the wait list group) and follow-up assessment (6 months, t5).

The reliability change index (RCI) will determine clinically significant change (Jacobson and Truax, 1991). The RCI will be calculated using the standard deviations at baseline and the test-retest reliability coefficient of the IPS (Guilera et al., 2018; Rozental et al., 2014). Participants will be classified as improved, deteriorated or no change based on the RCI for pretest and posttest measures.

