#### Exploratory analyses – covariates and moderators

2.9.3

Descriptive statistics will be used to describe the socio-demographic characteristics of the participants in terms of age, gender, ethnicity, marital status, and whether the participant is currently receiving any psychotherapy or medication. Descriptive statistics will also be used for data exploration on the outcomes of the CSQ-8, SUS, WAI-I and adherence. Additionally, these outcomes will be tested as predictors and moderators or treatment outcome. The moderation analyses will be conducted using PROCESS macro for SPSS version 3.4. The macro provides bias-corrected 95 % confidence intervals (CI) for the indices using a bootstrap calculation based on 5000 samples (Hayes, 2017).

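### Satisfaction, usability and alliance are tested as predictors but first measured together with the post-treatment IPS, so an association between them cannot be read in the direction the protocol states

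*Protocol article*

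**What the plan says.** Section 2.9.3 (Exploratory analyses) first plans descriptive statistics for "data exploration on the outcomes of the CSQ-8, SUS, WAI-I and adherence" and then adds that "these outcomes will be tested as predictors and moderators or treatment outcome". It names no time point for the outcome.

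Section 2.7.3 gives the scales a direction. The CSQ-8 is "used to measure the effects of participants' satisfaction with the overall intervention on the treatment outcome". Parallel wording is used for the SUS-10 (usability) and the WAI-I (satisfaction with the e-coach).

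Table 1 marks the CSQ-8, SUS-10 and WAI-I at T2 and T4 only. Its note defines the visits as "T2: 4 weeks post baseline – intervention group; T3: 4 weeks post baseline – waitlist group; T4: 8 weeks post baseline – waitlist group". The IPS is marked at T0, T2, T3, T4 and T5. On mode of collection, section 2.7 says: "At each time point, the participants receive a link to the assessment questionnaire via email".

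Section 2.9.1 states for the primary model: "The post-treatment score will be used as the dependent variable". Section 2.7.3 also describes a single 0 to 100 usefulness item: "At the end of each module the participants respond to the question" about that module. This item is not among the variables named in 2.9.3.

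**The concern.** The protocol states a direction, from rating to outcome, but schedules both sides of the relation for the same questionnaire. A student whose procrastination has eased by T2 has reason to rate the program and the coach well at T2. The resulting correlation would look the same as one produced by a good alliance causing improvement. Adjusting for baseline IPS does not separate the two, because the reverse path runs through the change since baseline.

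What is at stake is interpretation. The introduction wants these analyses to help identify who benefits most, and the discussion wants them to guide improvement of the program. A rating that is partly a consequence of the outcome serves neither purpose, and effort on coaching or redesign could be misdirected.

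**Working it through.** **Timing, from Table 1** (its visit labels are used throughout)

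| Arm | First CSQ-8, SUS-10, WAI-I | Post-treatment IPS | Later IPS |
|---|---|---|---|
| Intervention | T2 (4 weeks) | T2 (4 weeks) | T5 (6 months) |
| Waitlist | T4 (8 weeks) | T4 (8 weeks) | T5 (6 months) |

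In both arms the ratings coincide with that arm's own post-treatment IPS. They precede only the T5 IPS. No earlier measurement of the three scales is scheduled.

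**The plan's own sample size** (section 2.8: d = 0.50, two-sided alpha 0.05, power 0.80, dropout 28%)

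- n per arm = 2 × (1.960 + 0.842)² / 0.50² = 62.8, so 63. This matches the plan.
- 63 / (1 − 0.28) = 87.5, so 88 per arm and 176 in total. This also matches.

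The point does not dispute these figures. It only borrows n = 63 as the number of completers per arm.

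**Illustration 1: same-visit test.** Assume the rating has no effect on outcome, but improvement drives the rating with correlation r. By Fisher's z, SE = 1/√(63 − 3) = 0.1291.

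| Assumed r | atanh(r) | z = atanh(r)/SE | Share significant at two-sided 5% |
|---|---|---|---|
| 0.2 | 0.2027 | 1.57 | about 35% |
| 0.3 | 0.3095 | 2.40 | about 67% |
| 0.4 | 0.4236 | 3.28 | about 91% |

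**Illustration 2: with baseline adjustment, and with T5 as outcome.** Simulation, 4,000 runs, n = 63, all variables on a standardised scale: post = 0.6 × baseline − 0.8 × improvement; rating = r × improvement + √(1 − r²) × noise; T5 = 0.6 × post + 0.8 × noise. The rating has no effect on anything. Share of runs with p < 0.05 for the rating:

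| r | Post-test IPS, adjusted for baseline | T5 IPS, adjusted for baseline | T5 IPS, adjusted for baseline and post-test |
|---|---|---|---|
| 0 | 5% | 5% | 5% |
| 0.2 | 34% | 12% | 5% |
| 0.3 | 66% | 23% | 6% |
| 0.5 | 99% | 53% | 5% |

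With 88 complete students the first column becomes 5%, 47%, 81% and nearly 100%.

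Two things follow. Baseline adjustment gives no protection. Moving to T5 is not enough by itself; post-test IPS must be in the model as well. The return to about 5% assumes that improvement reaches T5 only through the recorded post-test score. The IPS is not perfectly reliable (section 2.7.1 cites test-retest r = 0.84), so a little could still leak through in practice.

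**The case against.** *The outcome time point is not fixed.* Section 2.9.3 says only treatment outcome, and 2.9.1 assesses IPS at follow-up as well as post-treatment. The T2/T4 ratings do precede T5. This stands: the problem is certain only if post-treatment IPS is used. But that is the dependent variable 2.9.1 names, and 2.9.3 does not exclude it.

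*The percentages are close to circular.* They are the power to detect correlations that were assumed. This stands in full. A reader might infer that the trial is likely to report a spurious predictor, but the documents give no correlation between rating and improvement, and at r = 0.2 a positive result would not even be the more likely one.

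*Predictor often just means a regressor.* Fair for 2.9.3 on its own. It does not cover 2.7.3, where the wording is about effects.

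*The analysis is exploratory.* True, and the discussion promises only preliminary insights. That label warns of chance findings and multiplicity, not of reversed direction, and the limitations paragraph does not mention the latter.

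*Module ratings are no substitute.* A reader might take the per-module item as a ready, correctly timed replacement. It is not: it asks about usefulness, not usability or alliance, and the discussion itself calls it non-validated. Since 2.7.3 lists it under moderators and covariates, its absence from 2.9.3 is also weak evidence that it will go unused.

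*Adjusting T5 for post-test IPS changes the question.* Correct. Benefit that alliance produced during the program is already in the post-test score and is adjusted away.

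**Conclusion.** The point holds as a limit on interpretation. The protocol gives these three scales a direction of effect, and its schedule cannot support that direction when the outcome is post-treatment IPS. It does not show that any prediction analysis with these scales is invalid, because a T5 model in the right time order is available from the planned data.

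No size can be attached from the documents. The rates of 35%, 67% and 91% rest on assumed correlations of 0.2, 0.3 and 0.4, n = 63 and no true effect; they show only that a modest reverse path would be readily detected and could then be misread. The randomised comparison, the primary result and the sample size are untouched. Adherence, a count of modules completed, is outside this point, as is moderation of the between-arm effect.

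**What to change.** - In 2.9.3, report the relations of CSQ-8, SUS-10 and WAI-I with post-test IPS at the same visit as associations only, without a direction.
- In 2.7.3, drop the wording that has these scales measuring effects on outcome.
- Keep prediction claims for time-ordered models: T2 (intervention) or T4 (waitlist) scales against T5 IPS, adjusted for baseline and post-test IPS, described as prediction of change after treatment.
- Optionally, add the usefulness ratings of early modules as a predictor of post-test IPS adjusted for baseline. Label this perceived usefulness, and do not offer it in place of the SUS-10 or WAI-I.

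The cost is analysis wording, with no new data. The downsides should be stated: T5 is likely to have fewer respondents; the T5 model misses benefit already gained by post-test; and early module ratings exist only for students who completed those modules.

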## Discussion

3

To the best of our knowledge, this is the first randomized controlled trial to examine the effectiveness of an internet-based intervention guided by trained clinical psychology student e-coaches for procrastination in a student population. In addition, this study will examine whether the treatment has any effect on secondary outcomes such as depression, anxiety, stress, and quality of life. We anticipate that the program will be effective in reducing procrastination behaviors. We also expect improvement in depressive symptoms, anxiety, stress and quality of life as they are closely associated with procrastination (Sirois, 2007; Flett et al., 2016; Stead et al., 2010; Beutel et al., 2016).

The results from this high-quality and adequately powered trial will add to the scarce evidence on the effectiveness of a guided internet-based intervention for treating procrastination in university students. We believe this study could provide a flexible and low-intensity treatment for procrastination and prevent common mental health problems in students. A recent meta-analysis on e-health interventions showed that guidance by non-clinicians can be equally effective compared to guidance delivered by specialists and clinicians (Leung et al., 2022). Therefore, using trained psychology students as e-coaches provides a cost-effective and scalable treatment method. In addition, we believe that the systematic screening process, personalized feedback, and a platform to communicate with an e-coach are promising approaches to allow students to recognize a problem and facilitate treatment seeking behaviors (Czyz et al., 2013).

The current study also assess the participants' satisfaction with treatment and e-coaches, program usability and treatment adherence. This will enable us to improve our program and the treatment experience further. Furthermore, the potential moderating variables will give us preliminary insights into who would benefit most from the treatment. Finally, the effectiveness of the intervention is tested in the same setting as it will be implemented. Moreover, while the participants receive compensation for completing all questionnaires, they do not receive any compensation for completing the program. This allows us to examine the real-life efficacy, demand and appeal of *GetStarted*.

The study's results should be considered in light of the following limitation. First, it should be noted that participation in the trial was completely voluntary. Therefore, it could be possible that participants differed from non-participants on important characteristics such as pretreatment motivation and help seeking behaviors that are known to influence treatment outcomes (Patterson et al., 2019; Sansfaçon et al., 2020). Additionally, it could be possible that severe procrastinators “put off” their participation long enough to miss out on treatment entirely. Nevertheless, our study was adequately powered to address the research question and the participants are likely to be a good representation of students that are open to e-health interventions. Second, given the nature of procrastination, it is possible that the study could encounter several dropouts and treatment adherence issues (Rozental et al., 2015a). Therefore, participants will receive support from e-coaches to increase motivation and adherence. Third, while the comparison with an inactive control precisely distinguishes the impact of the intervention, it can also overestimate the effects of treatment (Furukawa et al., 2014). In this study, participants in both groups will have access to treatment-as-usual options. Therefore, the results can be attributed to the actual effectiveness of the program. Fourth, we will not be able to make long-term comparisons between treatment and WLC as the control group will have access to the program four weeks post-randomization. However, the 6-month follow-up will allow a long-term within-group comparison for sustained treatment effectiveness. Finally, we use self-report measures that reflect the self-assessments of actual behaviors but could also be contaminated by other factors such as willingness to report difficulties and overestimating difficulties (Steel et al., 2001). Moreover, we use a non-validated single-item measure to assess participants' satisfaction with each module. However, previous studies have demonstrated that single-item measures can be practical alternatives to multi-item scales (van Hooft, 2014).

A natural continuation of the study would be to compare *GetStarted* with an active control to confirm the study's results and to expand evidence on the effectiveness of this program. Furthermore, the addition of ecological momentary assessments can be beneficial in determining the chronology of change. Finally, the recruitment of participants with procrastination and comorbid depression or anxiety (as established by a diagnostic tool) could evaluate and confirm the transdiagnostic treatment potential of the program.

## Conclusion

4

This protocol describes the design of a randomized controlled trial to evaluate the effectiveness of a guided internet-based intervention (*GetStarted*) for treating procrastination. The results from this study can build evidence for the effectiveness of a guided internet-based intervention for treating procrastination in university students.

Should it be effective, *GetStarted* could provide a flexible, low intense and cost-effective treatment for procrastination and for the prevention of common mental health problems.
